### Sample size {14}

A sample size of 3000 has >99% power to detect a difference in SPPB change as small as 0.54 points (the MCID) between the two groups at a two-sided alpha of 0.05, assuming a common SD of 2.7 for the SPPB change, 20% non-compliance, 10% dropouts, and an interim analysis. The estimates for MCID and SD are based on observation of older acute care medical patients [43, 44]. Using these same assumptions, the power is still 92% for detecting a smaller difference of 0.35. Therefore, we expect ample statistical power for analyzing the primary outcome. The main reason for selecting this sample size is to ensure that the analyses of important secondary outcomes are not underpowered. The most important of these is discharge disposition, because even a small absolute difference in the number of patients discharged to home, as opposed to a skilled nursing facility, is clinically important. We will be able to detect a 7% difference in discharge to home vs. SNF with 98% power.

For other binary secondary outcomes (a combination of venous thromboembolism, pneumonia and falls, 30-day mortality, or 30-day readmission), the study will have 85% power to detect a 33% reduction assuming an 8% rate in the control group. Because these outcomes are not contingent on patient cooperation, we anticipate no dropouts. For secondary continuous outcomes such as length of stay, assuming 20% non-compliance rate, the power to detect a 4-h difference (0.167 days) is 95%.

Regarding the cost analysis, there is no accepted way of doing a power calculation. However, we tried adding $300 (an approximation of the cost of the intervention) to the costs of each of 1500 patients drawn randomly from a sample of 3000 Cleveland Clinic medical inpatients over the age of 65 with an AM-PAC 6-Clicks score between 16 and 20. We then performed a *t*-test on the log-transformed costs, as described in the economic analysis section, and we were able to detect the increase with a p-value of 0.03, indicating that should the intervention increase costs by an amount equal to the cost of the intervention, we should be able to identify it. Similarly, if the intervention decreases total costs by $300 or more (not including the costs of the intervention), we should have sufficient power to detect it.

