### Methods for additional analyses (e.g., subgroup analyses) {20b}

We will conduct three sensitivity analyses to account for (1) missing outcomes data, (2) treatment heterogeneity by site, and (3) the dose-response curve in the intervention group.

To identify the patients most likely to benefit from ambulating with a MT, we will build models separately for each treatment arm to predict the outcome of at least 1-point increase in the SPPB (i.e., beyond the minimal clinically important difference). Using the predicted probabilities resulting from these models, we will develop a Classification and Regression Tree (CART) that should identify subsets of patients likely to benefit, not benefit, or be harmed by the treatment. For example, the analysis might show that female patients aged >75 years who have an initial 6-Clicks score between 16 and 18 have an estimated treatment benefit of being 22% more likely to achieve the 1-point increase in SPPB. Essentially the tree will form risk groups of patients with shared characteristics that should receive a similar care recommendation.

We will estimate the total cost of the episode of care including the index admission (from hospital cost accounting systems) and all non-medication costs for the 30 days following enrollment (from Medicare claims) for all patients. For the intervention group, we will add the personnel costs for the MTs (hourly wages plus benefits). Since cost data are skewed, our cost estimates will be transformed and then compared between groups using the *t*-test.

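### The cost power statements are unsupported: one random split does not establish power for a $300 increase, a $300 gross saving is cancelled by the added technician cost, and log costs are tested where mean cost is the question

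*Protocol article*

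**What the plan says.** In Sample size {14}, the protocol article says that cost has no agreed power method and offers one exercise instead: "we tried adding $300 (an approximation of the cost of the intervention) to the costs of each of 1500 patients drawn randomly". The pool was a "drawn randomly from a sample of 3000 Cleveland Clinic medical inpatients over the age of 65" within the trial's 6-Clicks range. The test is given as follows: "We then performed a *t*-test on the log-transformed costs, as described in the economic analysis section". The outcome was "we were able to detect the increase with a p-value of 0.03", from which the article concludes that a cost increase equal to the intervention's own cost should be identifiable. It then extends the claim to savings, stating that power is sufficient "if the intervention decreases total costs by $300 or more (not including the costs of the intervention").

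Methods for additional analyses {20b} gives the planned cost comparison. The endpoint is the index admission plus 30 days of non-medication claims. On intervention cost it says "For the intervention group, we will add the personnel costs for the MTs (hourly wages plus benefits"). On the test it says "Since cost data are skewed, our cost estimates will be transformed and then compared between groups using the" t-test. No second comparison that leaves technician cost out is described.

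The question is put as overall episode cost (Objectives {7}), as the cost-effectiveness of employing a technician (Abstract, Background), and as programme cost set against possible savings (Discussion).

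**The concern.** Three things do not fit together.

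- **A p-value is used as power.** Power is the share of repeated trials that would reach significance. One split yields one p-value, which mixes the $300 shift with whatever chance imbalance that split produced.
- **The saving is stated gross, but the analysis is net.** The power sentence sets intervention cost aside, while the planned analysis puts it into the intervention arm.
- **The test and the question use different scales.** A t-test on log costs compares geometric means. Budget impact and cost-effectiveness need the difference in arithmetic means, because only the mean multiplies up to total spending.

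Cost is one of the three stated aims and is meant to inform hospitals' staffing decisions. If the power statements are believed, a non-significant cost result could be read as ruling out a $300 effect in either direction, which the article gives no basis for.

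**Working it through.** **Inputs.** p = 0.03, 1500 against 1500, a $300 shift and intervention cost of about $300 come from Sample size {14}. The addition of technician cost comes from Methods for additional analyses {20b}. The error rate, "at a two-sided alpha of 0.05", is stated for the primary outcome and is assumed here for cost. The article gives no mean or SD of cost, so the p-value itself cannot be reproduced.

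**1. What p = 0.03 implies.**
- Two-sided p = 0.03 gives z = Φ⁻¹(1 − 0.03/2) = 2.170.
- If the true signal equals that z, power = Φ(2.170 − 1.960) = Φ(0.210) = 58%. A noncentral t with 2998 degrees of freedom also gives 58%.
- Rounding of p (0.025 to 0.035) gives 61% to 56%. A one-sided p would give 47%.
- The implied standardised difference is 2.170 × √(2/1500) = 0.079. At that value, 80% power needs about 2,501 per arm and 90% about 3,347, against 1,500 available.

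**2. How little one split tells.** The observed z varies around the true signal with SD 1, so the 95% range for the signal is 2.170 ± 1.960, or 0.210 to 4.130.
- Lower end, both tails: Φ(0.210 − 1.960) + Φ(−0.210 − 1.960) = 0.040 + 0.015 = 5.5%.
- Upper end: Φ(4.130 − 1.960) = 98.5%.
- Equivalently, p ≤ 0.03 would turn up in 42% of splits if true power were 50%, and in 23% if it were 30%.

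**3. The $300 saving under the planned analysis.** Net difference = technician cost − gross saving.
- Gross saving $300: 300 − 300 = $0, so the test rejects at its error rate, 5%.
- Gross saving $600: 300 − 600 = −$300, the size of effect that the exercise considered.

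The 5% assumes that saving and technician cost are each about constant per patient.

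**4. Log scale against mean scale (illustration).** The article gives no cost distribution, so lognormal costs are assumed here, with mean $8,000 to $15,000, log-SD 0.6 to 1.0 and 1,500 per arm.
- A constant $300 increase has 25% to 74% power on the log test and 6% to 35% on a comparison of arithmetic means.
- With mean $10,000, a 3% proportional saving (0.03 × 10,000 = $300) plus $300 of added cost leaves mean cost unchanged. The log difference is nevertheless +0.013 to +0.046, and about 8% to 26% of trials would show a significant increase, where 2.5% would under no difference.

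These figures show only that the two scales answer different questions. They do not estimate this trial's power.

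**The case against.** The strongest reply is that little depends on the exercise. The article introduces it with a disclaimer about cost power, and the sample size was chosen for secondary outcomes, above all discharge disposition. Re-simulation would change sentences, not recruitment or conduct. This stands, and it limits the severity.

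On the saving, the article says $300 or more, so larger savings remain detectable, and $300 is itself approximate. The parenthesis may also refer to a comparison without technician cost, where the reasoning for an increase would carry over roughly in reverse. That reading is possible, but no such comparison is planned in the article, and the claim would still rest on the same single split.

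On the scale, a log t-test is a coherent choice for skewed data, the article never uses the term mean cost, and retransformation may be set out in a fuller document. The fair criticism is confined to what is stated: the named test does not estimate the quantities that the aims ask for.

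A reader might go further in three ways that the documents do not support.

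- **True power is 58%.** That is only what one p-value implies; the value is very poorly determined.
- **The exercise used inpatient costs alone.** The article says costs of inpatients and does not say which components were counted.
- **The planned test would report savings while mean spending rises.** Geometric and arithmetic means can diverge, but the article gives no cost distribution from which such a reversal could be shown to be likely here.

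**Conclusion.** The point holds in three limited parts.

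- Power to detect a $300 increase is not established: 58% at face value, with a range of about 5.5% to 98.5%, assuming a two-sided 5% test.
- The claim of sufficient power fails at a gross saving of $300 under the only planned comparison, where rejection is about 5%. About $600 gross is needed for a $300 net difference, taking the article's own $300 as the technician cost.
- The planned test addresses geometric mean cost, whereas the aims concern arithmetic mean cost. This rests on reading overall cost, cost-effectiveness and cost against savings as mean quantities, which is their ordinary meaning.

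This should be fixed. It does not threaten the trial's sample size or its primary outcome, because cost drives neither.

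**What to change.** 1. Repeat the random split at least 1,000 times on the same 3000 records, using 30-day episode cost if it is available. Report the share of significant results, or the expected confidence interval width, in place of the single p-value.
2. Restate the saving sentence net of technician cost. Alternatively, say that it refers to a separate comparison excluding that cost, and add that comparison to Methods for additional analyses {20b}.
3. Make the difference in arithmetic mean 30-day cost, including technician cost, the main cost estimate, with a bootstrap confidence interval or a gamma log-link model. Keep the log t-test as supportive.

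The cost is a few hours of re-simulation on data already held, plus wording changes; recruitment and data collection are untouched. The downside is that the stated precision for cost will look less favourable.

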### Recruitment {15}

Recruitment will be conducted by the MTs at the various study sites. At 7 am each morning, we will provide the MTs with a list of potentially eligible patients based on a computer query of current patients. The MTs will then review the EHR for additional eligibility criteria. Based on our pilot, approximately 1 in 6 patients will qualify for the study and most can be excluded through chart review. MTs will then approach potentially eligible patients to ask if they might be interested in participating in the study. Interested patients will be screened for eligibility and, if they meet criteria and consent, will be enrolled into the study. Based on both the Cleveland Clinic and Baystate pilots, we expect that at least 50% of the eligible patients approached will consent to participate. This rate does not reflect the acceptability of the intervention, which has been almost universal in our non-randomized pilots. Rather, it reveals patients’ hesitance to participate in clinical trials in general, including having to wear the accelerometer, share medical data with the study team, complete physical testing at baseline and at discharge, and report on mobility, frailty, and ADLs at 30 days, with only a 50% chance of receiving the active intervention. Our goal is to recruit 200 patients per year at each hospital. This represents approximately 1–2% of all medical admissions (depending on the hospital size). As a result, we anticipate there will be plenty of patients available for recruitment on any given day. MTs will be expected to recruit 4 patients per week or approximately 1 patient every other day. They should have sufficient time to provide ambulation assistance for 4 patients daily, but will generally have 2 or 3 patients to assist.

## Assignment of interventions: allocation

### Sequence generation {16a}

Randomization will be done using a computerized system. A block randomization scheme with a size of 4 will be used to ensure approximately equal numbers of patients per group. Allocation will be stratified within units within hospitals.

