### Concealment mechanism {16b}

The block size will not be disclosed to study staff who are enrolling patients.

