### Implementation {16c}

The allocation sequence is determined a priori by a biostatistician. The MT will be responsible for the randomization process and patient allocation.

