## Assignment of interventions: blinding

### Who will be blinded {17a}

Blinding of patients and MTs to the intervention is not possible. However, outcomes at hospital discharge and after discharge will be collected by assessors blinded to allocation.

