## Data collection and management

### Plans for assessment and collection of outcomes {18a}

#### Primary outcome: Short Physical Performance Battery

The initial SPPB will be administered by the MT enrolling the patient as part of the baseline assessment. The final SPPB will be administered by a physical therapist or exercise physiologist blinded to the patient’s treatment group allocation. All assessors will be trained by the primary study physical therapist ([name]). Acceptable inter-rater reliability of the SPPB has been shown in prior studies, [59, 60] but we will assess inter-rater reliability for the first 10 patients enrolled with each mobility tech as a quality check; the primary study physical therapist ([name]) will be the second assessor.

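### One fixed block size of 4 per unit, published during open recruitment, weakens concealment from the unblinded mobility technicians who also score the baseline SPPB

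*Protocol article*

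**What the plan says.** Sequence generation {16a} specifies a computerised system and one block size: "A block randomization scheme with a size of 4 will be used to ensure approximately equal numbers of patients per group". It adds: "Allocation will be stratified within units within hospitals". Recruitment {15} implies a 1:1 ratio, since patients join "with only a 50% chance of receiving the active intervention".

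Concealment mechanism {16b} states: "The block size will not be disclosed to study staff who are enrolling patients". Implementation {16c} says that a biostatistician fixes the sequence in advance, and then: "The MT will be responsible for the randomization process and patient allocation".

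The MT has several other roles. "Recruitment will be conducted by the MTs at the various study sites", and the MT also takes consent (section {26a}) and delivers the walks (section {11a}). On the primary outcome measure, section {18a} says: "The initial SPPB will be administered by the MT enrolling the patient as part of the baseline assessment". Under section {17a}, "Blinding of patients and MTs to the intervention is not possible". A blinded physical therapist or exercise physiologist scores the final SPPB.

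The primary outcome is the change from that baseline, compared by an independent-samples t-test. A mixed model is used only if relevant baseline imbalance appears (section {20a}). Trial status gives 15 May 2023 as the start of recruitment and 31 May 2026 as its expected end.

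**The concern.** Concealment requires that the person enrolling the next patient cannot foresee the next allocation. A computerised list keeps future entries out of sight. With a constant block size, however, past entries can be enough to work out the next one. The last place in each block of 4 is always determined, and the third is determined whenever the first two match. The article names withholding the size as a safeguard and then prints the size where enrolling staff can read it.

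Two routes to bias follow:

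- **Selection.** Recruitment {15} expects more candidates than the roughly one enrolment every other day, so the MT has some choice of whom to approach and when.
- **Ascertainment.** The MT's baseline score is subtracted in the primary outcome. A score shaded downwards in patients expected to receive the intervention inflates their change, and blinding the final assessor protects only the other half of the subtraction.

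**Working it through.** The article gives no predictability figure, so there is none to reproduce. The check counts what a fixed block of 4 reveals.

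**Inputs.** Block size 4 and stratification by unit (section {16a}); 1:1 ratio (section {15}); 3000 patients, with 0.54 points as the MCID and 0.35 as a smaller detectable difference (section {14}); five hospitals with two MTs each (section {9}).

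**Predictability in a complete block.** There are 6 equally likely orders of two A and two B. A place is determined once one arm has used both of its places. The best guess is the arm with more places left.

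| Place | Pr(determined) | Pr(best guess correct) |
|---|---|---|
| 1 | 0 | 1/2 |
| 2 | 0 | 2/3 |
| 3 | 1/3 | 2/3 |
| 4 | 1 | 1 |
| Mean | (1/3 + 1)/4 = 33.3% | (1/2 + 2/3 + 2/3 + 1)/4 = 17/24 = 70.8% |

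For a block of 2m, the determined share is 1/(m + 1), which gives 1/3 at m = 2. Without blocking, guessing succeeds 50% of the time.

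**Incomplete blocks.** The number of units is not stated, so this is a range over assumed counts. Each hospital would enrol 3000/5 = 600.

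- 10 units of 60 patients: all blocks complete, 33.3%.
- 20 units of 30: 7 complete blocks plus 2 patients, (7 × 4/3)/30 = 31.1%.
- 60 units of 10: 2 complete blocks plus 2 patients, (2 × 4/3)/10 = 26.7%.

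**Illustrative bias.** Suppose baseline is scored s points too low in the predictable third of the intervention arm and nowhere else. The spurious difference in mean change is s × 1/3. The documents give no value for s, so a range is shown.

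| Assumed s | Bias in SPPB change (points) |
|---|---|
| 0 | 0 |
| 0.25 | 0.08 |
| 0.5 | 0.17 |
| 1 | 0.33 |

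The top of this range is close to the 0.35-point difference used in the sample size section.

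**Effect of other block schemes.** Fixed sizes come from enumeration. Mixed sizes come from a simulation of 20,000 blocks, with a guesser who knows the candidate sizes.

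| Scheme | Certain | Best guess correct |
|---|---|---|
| Fixed 4 | 33.3% | 70.8% |
| Fixed 6 | 25.0% | 68.3% |
| Fixed 8 | 20.0% | 66.6% |
| Random 4/6 | about 5.8% | about 69% |
| Random 4/6/8 | about 2.4% | about 68% |

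Varying the size nearly removes certainty but barely changes guessing.

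**Reach of the inter-rater check.** It covers the first 10 patients of each MT. With 5 × 2 = 10 MTs and no turnover (an assumption), that is 100 of 3000 patients.

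**The case against.** The strongest reply is that predictability is conditional. The MT must learn or infer the block size and must track allocations unit by unit. A reader might infer that one in three allocations simply is predictable, or that MTs know every past allocation on their units. The documents support neither. No section assigns MTs to units, the two MTs at a hospital would have to share or look up allocations, and about four enrolments a week per hospital are spread over an unstated number of units. A block could take weeks to fill.

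A reader might also infer that withholding the block size is the only concealment measure. It is not, because there is a computerised system and a list set in advance by a biostatistician. Nothing says that the MT sees the list. This part of the reply stands, and it narrows the weakness to inference from past allocations.

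Other safeguards count too. The SPPB is a performance test, assessors are trained, the primary study physical therapist double-scores each MT's first 10 patients, and a daily computer query generates the candidate list. These reduce the room for bias but do not close it. The double-scoring covers a small share of patients, and it comes early, before an allocation pattern could be learned.

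Finally, a lock on baseline data before allocation may already exist. Section {13} places baseline assessment and randomisation together at T0 without giving their order, and an article may leave system settings to the full protocol. The absence of a lock is therefore not established.

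**Conclusion.** The point holds as a design weakness that is cheap to improve. One constant block size, printed during open recruitment, undercuts the article's own safeguard, and the staff best placed to exploit it also score the baseline half of the primary outcome. For an MT who knows or infers the size and tracks the unit, up to 33.3% of allocations are certain (about 27% to 33% over the assumed unit counts) and about 71% can be guessed in complete blocks.

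It would be tempting to conclude that the trial carries a bias of about 0.17 points, roughly 30% of the 0.54-point MCID (0.17/0.54 = 31%). The documents do not support that. The figure depends on an assumed 0.5-point shading of every predictable intervention patient, and no shading gives no bias. The risk of selective approach or shaded scoring is potential, not demonstrated.

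**What to change.** For all blocks not yet opened, regenerate the list with randomly varying block sizes (for example 4, 6 and 8), and do not publish the new sizes until recruitment closes. Certain allocations fall from 33% to about 2%, but best-guess success stays near 68%, so this is an improvement and not a complete cure.

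Confirm also that the system releases an allocation only after consent, eligibility and the baseline SPPB have been entered and locked. This prevents scoring once the allocation is known. It does not prevent shading by anticipation, which happens before the lock. Closing that route as well would need a baseline scorer who does not know the unit's past allocations.

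The cost is a new list for unopened blocks and a check or change of a system setting. The downside is a slightly larger possible imbalance within small units: an unfinished block can leave the arms up to 4 apart at size 8, against 2 at size 4. That is trivial at 3000 patients.
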